### Outcome measures

The primary outcome measures of the trial will be the number of new leprosy cases detected, the number of child cases detected, and the incidence rate ratios of each arm compared with 2019 baseline. These will be measured at the two-year follow-up of the trial. In addition, the cost-effectiveness and acceptability of PEP++ as a preventive intervention will be measured as separate side studies. The added value of geospatial methods will be measured by the proportion of new leprosy cases in clusters and non-clusters.

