**Methods:**

The PEP++ study is a cluster-randomised controlled trial in selected districts of India, Brazil, Bangladesh, and Nepal. Sub-districts will be allocated randomly to the intervention and control arms. Leprosy patients detected from 2015 − 22 living in the districts will be approached to list their close contacts for enrolment in the study. All consenting participants will be screened for signs and symptoms of leprosy and tuberculosis (TB). In the intervention arm, eligible contacts receive the enhanced PEP++ regimen with three doses of rifampicin (150 − 600 mg) and clarithromycin (150 − 500 mg) administered at four-weekly intervals, whereas those in the control arm receive SDR-PEP. Follow-up screening for leprosy will be done for each individual two years after the final dose is administered. Cox’ proportion hazards analysis and Poisson regression will be used to compare the incidence rate ratios between the intervention and control areas as the primary study outcome.

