### Sample size

The calculation of the sample size is based on the primary objective to find differences in new case detection rates (NCDR). The first is a difference in NCDR in the population in the intervention area after four years, compared to the baseline rate in 2019. The year 2019 is selected as the baseline to avoid any effect of the COVID-19 pandemic. The second is the difference in incidence rates in the contact groups between the close contacts who have received PEP++ and controls who have received SDR-PEP.

The sample size calculation for the difference in rates in the close contacts is based on the NCDR found in contacts in the COLEP trial sample. The NCDR in the SDR intervention group was 291/100,000 over 2 years, or an annual rate of 146/100,000. To reduce this rate by 50%, using a power of 90%, a significance level of 0.05, design effect of 1.5, correction for non-eligibility of 25% and loss to follow-up of 25%, we aimed to enrol 202,360 close contacts. This should result in giving PEP to at least 162,000 participants.

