### Data analysis

Data from the PEP++ trial will be analysed primarily through quantitative methods using descriptive analysis for all variables. Table 3 outlines the tools to be used to measure and analyse the study outcomes.

**Table 3 Tab3:** PEP++ project outcomes and statistical analysis plan

Objective	Outcome	Hypothesis	Outcome measure	Method of analysis
To provide evidence of the effectiveness of an enhanced post-exposure prophylaxis regimen (PEP++) compared to SDR-PEP	Primary: contacts diagnosed with leprosy	PEP++ offers a higher protection against leprosy disease manifestation than SDR-PEP	Number of persons with leprosy disease detected at 24 months after receiving prophylaxis	Descriptive statistics; Cox’ proportion hazards analysis and Poisson regression comparing rates between the intervention and control areas
To show the cost- benefit and acceptability of the enhanced chemoprophylaxis regimen	Secondary: Cost–benefit of the enhanced regimen compared with effectiveness of SDR-PEP	PEP++ is a cost-effective strategy in leprosy control and the increased effectiveness of the intervention will justify additional costs from multiple doses	Number of contacts screened, cases prevented, and disabilities avoided against operational costs and out-of-pocket expenses	Health economic evaluation
	Secondary: Acceptability of the enhanced regimen compared with SDR-PEP	The new regimen will be accepted by contacts and health professionals	Proportion of eligible close contacts who take all three doses; qualitative interview results indicating that PEP++ is acceptable	Descriptive statistics of contacts who took medication; qualitative content analysis of interviews; semi-structured interviews, FGDs
To provide evidence of increased transmission of *M. leprae* in cluster areas identified through GIS-based mapping compared to non-cluster areas	Secondary: Contacts diagnosed with leprosy in identified high-transmission clusters (2014–19 index cases)	Detection of new leprosy cases will be higher in the cluster areas than in non-cluster areas due to higher local transmission and relative risk	Rate ratios of all new leprosy cases and child cases in cluster areas as compared with non-cluster areas (as a result of intervention as well as passive cases); rate ratio	Poisson regression comparing rates between cluster and non-cluster areas

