To demonstrate the effectiveness of the community education and behaviour change interventions to change the perception of leprosy in the study districts	Secondary: Levels of knowledge, attitudes, and stigma in each district	New, contextualised education materials and interventions will increase community knowledge regarding leprosy and reduce stigma so as to promote early detection	Change in KAP, EMIC-CSS and SDS scores and interviews/FGDs in all four target groups	Descriptive statistics; comparison of mean/median scores between baseline and end-line surveys; effect size; correlations between exposure to the interventions and KAP, EMIC-CSS and SDS scores; multivariate regression; qualitative content analysis of interviews, FGDs, and observations
To demonstrate proof of concept of the potential for the PEP++ approach to reduce, and ultimately stop, the transmission of *M. leprae* in a target area	Primary: Detection of new autochthonous child cases of leprosy	Reduction in new case and child case detection will be higher in intervention compared with control areas; Overall and child case detection levels will reduce against baseline (2019) detection	Rate ratio of new case and child case detection per 1,000,000 population; total number of new cases per district	Descriptive statistics, comparison of new case and child case detection rates between the intervention and control areas

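### The primary outcome is stated inconsistently: the Outcome measures section sets each arm against 2019, while the abstract, Table 3 and the sample size shown rest on intervention versus control

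*Protocol article*

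**What the plan says.** All places are in the protocol article.

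- **Objectives.** The primary objective is the effectiveness of PEP++ compared with SDR-PEP.
- **Abstract, Methods.** Cox and Poisson models will be used "to compare the incidence rate ratios between the intervention and control areas as the primary study outcome".
- **Outcome measures.** "The primary outcome measures of the trial will be the number of new leprosy cases detected, the number of child cases detected", and, as the third item, "the incidence rate ratios of each arm compared with 2019 baseline". On timing: "These will be measured at the two-year follow-up of the trial".
- **Sample size.** Two differences are listed under the primary objective. "The first is a difference in NCDR in the population in the intervention area after four years, compared to the baseline rate in 2019". The second is the difference in incidence between contacts given PEP++ and contacts given SDR-PEP. The calculation shown is for the second.
- **Table 3, first row.** "Primary: contacts diagnosed with leprosy", counted at 24 months after prophylaxis, with rates compared between intervention and control areas.
- **Table 3, last row.** "Primary: Detection of new autochthonous child cases of leprosy", under a separate objective on reducing transmission in an area. Its hypotheses are stated both between areas and against 2019.

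**The concern.** The section that defines the primary outcomes should name the contrast that answers the primary objective. The only contrast it names sets each arm against its own past. Both arms could improve on 2019 with no difference between the regimens, and an arm could fail to improve although its regimen is better.

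The article itself gives reasons to expect detection to change for causes other than PEP++. All consenting contacts in both arms are actively screened. SDR-PEP blanket campaigns follow in clusters, with the aim of lowering incidence in the population. Community education runs in the implementation areas. The Sample size section chose 2019 in order to avoid an effect of COVID-19, which concedes that detection rates shift over calendar time.

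At stake is what the trial may conclude. If the Outcome measures section is followed as written, the headline result would be a non-randomised comparison, although the trial was randomised and, on the calculation shown, sized for the randomised one.

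**Working it through.** **1. The statements side by side**

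| Place | Population | Contrast | Time |
|---|---|---|---|
| Objectives | not specified | PEP++ vs SDR-PEP | not given |
| Abstract | areas | intervention vs control | screening two years after final dose |
| Outcome measures, items 1 and 2 | not specified | none named (all cases; child cases) | two-year follow-up |
| Outcome measures, item 3 | each arm | arm vs 2019 | two-year follow-up |
| Sample size, first difference | population, intervention area only | vs 2019 | four years |
| Sample size, second difference | close contacts | PEP++ vs SDR-PEP | not given |
| Table 3, first row | contacts | intervention vs control | 24 months |
| Table 3, last row | population, with child cases | between areas and vs 2019 | not given |

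The contact outcome is at two years wherever a time is given. The time conflict is confined to the population comparison with 2019.

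**2. Which contrast the stated sample size belongs to**

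Inputs from the Sample size section: control rate 146/100,000 per year, 50% reduction, power 90%, significance level 0.05, design effect 1.5, non-eligibility 25%, loss to follow-up 25%. Assumed because not stated: two-sided test, 1:1 allocation.

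Per arm, with p1 = 0.00146, p2 = 0.00073 and mean p = 0.001095:

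n = [1.960·√(2p(1−p)) + 1.282·√(p1(1−p1) + p2(1−p2))]² / (p1 − p2)² = 43,132

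- Both arms: 2 × 43,132 = 86,264
- Design effect: 86,264 × 1.5 = 129,396
- Two allowances of 25%: 129,396 × 1.25 × 1.25 = 202,181

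The article states 202,360, a difference of 179 or 0.09%. The match is not unique: a one-sided, continuity-corrected version that divides by 0.75² gives 201,835. That version too is the contact comparison at 0.05. (Whether the annual rate and the factor 1.25 are the right inputs is a separate matter.) The article shows no calculation for the comparison with 2019 or for child cases.

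**3. Why a ratio to 2019 does not answer the objective**

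Take the plan's own 50%. Suppose detection halves in both arms from equal 2019 rates. Each arm's ratio to 2019 is 0.5, which looks like success twice. The between-arm ratio is 0.5 / 0.5 = 1, so PEP++ adds nothing to SDR-PEP.

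**4. Conditional error and power**

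This applies only if several outcomes stay primary, each is tested at 0.05, and any one may declare success.

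- Three independent tests: 1 − 0.95³ = 0.143
- Four independent tests: 1 − 0.95⁴ = 0.185

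Positive correlation lowers both figures. If 0.05 were instead split equally over three, power for the contact comparison at 202,360 would fall from 90% to 80.2%. Keeping 90% would take about 259,950 contacts on the article's own inflation factors.

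**The case against.** The strongest reply is that most of the article agrees with itself. The objective, the abstract, the second sample-size difference and the first row of Table 3 all point to the between-arm comparison, and the third item in Outcome measures is the outlier. A reader might infer that the deciding result is wholly open. The documents do not support that: the intended comparison can be recognised. What stands is that the defining section does not state it.

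It can also be said that there are two levels of outcome, each with its own primary. Table 3 ties its two primary labels to different objectives, the Discussion foresees individual- and population-level analyses, and the child-case row includes an intervention-versus-control hypothesis. This is a legitimate design, so child cases need not be demoted. The article does not say, however, that the population-level outcome leaves the regimen question untouched.

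The abstract could even be read as comparing the two arms' ratios to 2019 with each other. That would use the randomisation, but it is another quantity, at area level, and not the one sized.

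Three stronger readings should be resisted:

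- *That alpha is uncontrolled.* The article states no rule, but a multiplicity rule commonly sits in the analysis plan, which is not shown. The significance level of 0.05 is attached only to the contact calculation.
- *That the trial's false-positive risk is 14% to 19%.* Those figures need independent tests and success on any one. Child cases are a subset of all cases, and no such success rule is stated.
- *That only one contrast was ever sized.* The article shows one calculation; the full protocol may hold another.

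Four years might also mean intake plus two years of follow-up. The text does not say so.

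**Conclusion.** The inconsistency is real and should be corrected before analysis. As written, the Outcome measures section makes a non-randomised before-after ratio primary and names no PEP++ versus SDR-PEP contrast. The objective, the abstract, the first row of Table 3 and the only calculation shown rest on intervention versus control. Two lesser ambiguities go with it: the standing of population child-case detection, and two years or four for the population comparison with 2019.

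The consequence is one of interpretation rather than of a fixed number. A favourable ratio to 2019 could be reported as the primary result without evidence that PEP++ outperforms SDR-PEP. The error inflation in step 4 is conditional and is not an estimate for this trial. The reproduction of 202,360 assumes a two-sided test and equal allocation.

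**What to change.** 1. In Outcome measures, state the primary outcome for the regimen objective as leprosy diagnosed in close contacts by the two-year follow-up, PEP++ versus SDR-PEP, as a between-arm rate ratio. Use the same wording in the abstract, the Sample size section and Table 3, and say contacts rather than areas where contacts are meant.
2. Label every comparison of an arm with 2019 as secondary or descriptive.
3. State whether population child-case detection is secondary, or a separate population-level primary that does not decide the regimen question.
4. Give the population outcome one time point, and say from what date it is counted.
5. If more than one outcome stays primary for the same claim, point to the rule that governs them, in the analysis plan or here.

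The cost is wording in the protocol, with the registry entry brought into line. With a single primary for the regimen question, the planned 202,360 contacts and the 90% power are unchanged on the plan's own inputs, and no data collection changes.

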### Intervention implementation

Post-exposure prophylaxis will be offered to all eligible participants. Those in the intervention arm will receive three doses of RMP/CLR (PEP++ regimen) with four-week intervals. To increase the acceptability and reduce the potential adverse events, extended-release clarithromycin will be offered where available for purchase. An additional four-week tolerance exists for each repeated dose so that an interval of eight weeks between doses is valid. Participants in the control arm will receive SDR-PEP. The medication dosages of the PEP++ and SDR-PEP regimens per age group are presented in Table 2. Both regimens will be provided only under supervision of the research staff and/or medical officers. The date, dosage and type of PEP will be recorded for each eligible person in the study.

**Table 2 Tab2:** PEP +  + regimen dosage by age group

	**PEP++ regimen**^**a**^	**SDR-PEP**
≥ 15 years	600 mg RMP + 500 mg CLR	600 mg RMP
13–14 years	450 mg RMP + 500 mg CLR	450 mg RMP
10–12 years	450 mg RMP + 450 mg CLR^b^	450 mg RMP
6–9 years	300 mg RMP + 300 mg CLR^b^	300 mg RMP
2–5 years	150 mg RMP^b^ + 150 mg CLR^b^	150 mg RMP^b^

^a^A four-weekly dose at day 1, 29 and 57 with four-week tolerance (up to 56 days between doses)

^b^ml equivalent in paediatric suspension or capsules, depending on availability

The risk of inducing rifampicin resistance in *M. leprae* or *M. tuberculosis* after providing a single dose of rifampicin is considered negligible because only repeated doses of a single antibiotic will increase the risk of resistance [15]. Moreover, participants that have received rifampicin in the last two years or that show any signs or symptoms of TB or leprosy will not receive PEP. Contacts confirmed to have TB or leprosy will be treated according to the national guidelines.

### Leprosy perception

A person’s perception of leprosy can negatively affect health-seeking behaviour and the acceptance of new interventions [16]. Therefore, contextualised community education and behaviour change (CEBC) materials are developed as part of the study to change the perception (knowledge, attitudes, beliefs, and emotions) regarding leprosy and reduce stigma, as well as to increase the community acceptance of preventive treatment. First, a leprosy perception study was conducted in each country to investigate the perceptions of leprosy patients, contacts, community members and health workers regarding leprosy, i.e., the way people see leprosy, what they know about leprosy and their attitudes, beliefs and reported behaviour towards persons affected by leprosy [17, 18]. A mixed-method approach will be used to measure the perception, including in-depth interviews, focus group discussions (FGDs), the knowledge, attitudes, and practices (KAP) tool, the Explanatory Model Interview Catalogue Community Stigma Scale (EMIC-CSS) and the Social Distance Scale (SDS). During a workshop, leprosy affected persons and other key stakeholders will use the outcomes of the perception study to develop messages for the CEBC materials. The CEBC materials will be distributed throughout the implementation areas and piloted before the start of the trial [19].

### Geospatial methods

Prior to the trial implementation, geospatial analysis was done to develop epidemiological maps and determine the target areas for blanket campaigns. The latitude and longitude of all patient’s residents registered from 2015 to 2021 were collected using the mobile application MapitPro (version 7.6.0). All data points were checked for clustering in open-source Quantum Geographic Information System (QGIS) version 3.4.1 (QGIS Developer team, Madeira (2018)). A contextualised spatial analysis approach was developed to identify small and precise clusters in each implementation area. This approach included non-statistical geospatial methods combined with expert consultation. During the expert consultations, country-specific definitions of a cluster were determined considering the local context [20].

### Blanket campaigns

As predicted by mathematical modelling, a larger reduction in new cases detected can be achieved by implementing additional blanket campaigns in the identified clusters. For each index case in a cluster, the households not listed as close (neighbour) contacts within a radius of approximately 100 m will be visited until 80 to 100 participants (blanket contacts) are included in the study. If this results in over 80% of the cluster area being covered, then the entire population will be invited for participation. These blanket contacts are, similar to the close contacts, asked for consent to participate in the trial, screened for signs and symptoms of leprosy and when eligible, are provided SDR-PEP.

### Data collection

Data collection will be done offline using the Research Electronic Data Capture (REDCap) system created at Vanderbilt University in the United States. Specific forms and modules were developed by the study teams, translated to the local languages, and downloaded to tablets and smartphones for field usage. First, a unique identification code (UIC) will be created for each close contact in the trial to anonymise the data. The UIC is linked to the index case and will be used to link the different data collection forms that will be created for each contact. Contacts are then visited at home and asked to sign a consent form if they are willing to participate. Disclosure of the identity of the index case is avoided whenever possible when approaching neighbours and social contacts.

From all contacts, we will collect demographic data (e.g., name, age, gender), information on the relationship with the index case and the results from the screening and eligibility questions in the close contact registration form. The date and dosage of the PEP administered is recorded in either the SDR-PEP form or PEP++ forms (i.e., first, second and third dose). Moreover, any side effects or adverse events due to SDR-PEP or PEP++ will be registered in the adverse event form. During the trial, the GPS coordinates of all participants and new leprosy patients will be collected to determine the spatial effectiveness of PEP. all case records and GPS data are stored temporarily on the mobile study devices and uploaded daily to a national server in each country.

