## Methods and design

### Objectives

The primary objective of the PEP++ randomised controlled trial (RCT) is to provide evidence of the effectiveness of an enhanced post-exposure prophylaxis regimen (PEP++) compared to the currently recommended regimen of SDR-PEP. Each study district will have an adverse events committee to monitor the frequency and severity of such events in each study arm and ensure participant safety.

Secondary study objectives seek to provide evidence of:The acceptability and cost-effectiveness of PEP++ as a preventive interventionThe accuracy of geospatial methods to identify target areas for blanket campaigns, andThe effectiveness of community education and behaviour change (CEBC) interventions to change the perception of leprosy and reduce stigma

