### Study design

The study will use a cluster-randomised non-blinded controlled trial design with two arms to compare the effectiveness of three doses of RMP/CLR (the PEP++ regimen) with SDR-PEP in the prevention of leprosy disease among contacts of newly diagnosed leprosy patients. The randomisation units will sub-district divisions in each country context that will be randomly allocated to the two study arms.

All eligible leprosy patients in the districts will be asked to enumerate their close contacts. These individuals will subsequently be approached and enrolled in the study. Those contacts who provide informed consent are screened for signs of leprosy and tuberculosis and for inclusion eligibility. Contacts of leprosy patients living in the intervention arm receive the PEP++ regimen while those in the control arm receive SDR-PEP. All participants included in the study will be followed up two years after receiving the final dose of PEP++ or SDR-PEP.

The residences of the leprosy cases approached for the study will be geocoded in order to develop epidemiological maps that identify clusters of leprosy cases. After the regimen trial intake is concluded, blanket campaigns with SDR-PEP will be implemented in these clusters (high-risk areas) to reduce leprosy incidence at the population level. The study schedule is presented in Fig. 1. A checklist of Recommendations for Clinical Intervention Trials (SPIRIT) is also available (Supplementary file 1).

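### Adverse events enter the form only if attributed to the drug, in an open-label trial whose committees monitor frequency by arm; early contact may also differ between arms

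*Protocol article*

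**What the plan says.** Safety monitoring appears beside the primary objective (protocol article, Objectives): a committee in each study district is to "monitor the frequency and severity of such events in each study arm and ensure participant safety".

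The only recording rule in the text is in Data collection: "any side effects or adverse events due to SDR-PEP or PEP++ will be registered in the adverse event form". Neither section says who decides that an event is due to the regimen.

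Study design describes a "cluster-randomised non-blinded controlled trial design with two arms". Intervention implementation says of dosing that "Both regimens will be provided only under supervision of the research staff and/or medical officers". For PEP++, footnote a to Table 2 gives "A four-weekly dose at day 1, 29 and 57 with four-week tolerance (up to 56 days between doses"; for the comparator, "Participants in the control arm will receive SDR-PEP", a single dose. After dosing, Study design states one contact for everyone: "All participants included in the study will be followed up two years after receiving the final dose of PEP++ or SDR-PEP". The Abstract describes that visit as screening for leprosy and does not mention adverse events.

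Outcome measures and Table 3 contain no adverse-event outcome and no comparison of safety between arms. The schedule of assessments is in Fig. 1, which is not shown.

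**The concern.** The committees are to follow how often events occur, and how severe they are, in each arm. The stated rule makes those counts depend on two things other than the drug.

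The first is attribution. If an event is registered only once someone has judged it due to the regimen, the count cannot then be used to judge whether the regimen causes events. Nothing in the text shows that the person judging is masked to the regimen. Intervention implementation also says that extended-release clarithromycin is offered partly to limit adverse events, so staff may be readier to attribute an event to PEP++. Conversely, an unexpected event that nobody suspects has no stated route to the committee in either arm.

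The second is opportunity to report. On the visible text, PEP++ contacts meet staff again within weeks of doses 1 and 2, and control contacts do not.

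A committee could therefore read an excess in PEP++ as harm when part of it comes from attribution or contact, or could fail to see a real excess. Tolerability of three two-drug doses against one single-drug dose bears directly on whether PEP++ should replace SDR-PEP. The primary leprosy outcome is not affected.

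**Working it through.** The document states no figure on this point, so there is none to reproduce. The check compares the relevant statements, counts contacts, and adds a labelled illustration.

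**1. Attribution.** Let *E* be the number of events of some kind in an arm, and *a* the probability that such an event is judged due to the regimen. The registered count is *E* × *a*, so

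registered ratio = true ratio × (*a* in PEP++ ÷ *a* in control).

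This equals the true ratio only if *a* is the same in both arms. In an open-label trial nothing in the text secures that. Because unattributed events are not counted under the rule as worded, *a* cannot be estimated afterwards and the counts cannot be corrected. If *a* is close to zero in both arms, as for an unexpected event, the registered count is close to zero whatever the true difference.

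**2. Contacts after a dose, from the visible text.**

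| | PEP++ | SDR-PEP |
|---|---|---|
| Supervised doses | 3 (days 1, 29, 57) | 1 |
| Contacts that follow an earlier dose, before two years | 3 − 1 = 2 | 1 − 1 = 0 |
| Time from previous dose to that contact | 28 days on schedule (29 − 1; 57 − 29), up to 56 | none stated |
| Contact between last dose and two years | none stated | none stated |
| Visit two years after final dose | 1 | 1 |

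**3. Illustration (all inputs assumed, none from the document).** Give every dose in both arms the same event risk *p* = 0.05. Let capture be *c* = 0.9 when a dose visit follows and *s* when none does. Doses 1 and 2 of PEP++ have capture *c*; dose 3 of PEP++ and the single control dose have capture *s*.

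- Recorded ratio per dose = [(2*c* + *s*)/3] ÷ *s*. The true value is 1.0.
- Recorded ratio per person = [1 − (1 − *pc*)²(1 − *ps*)] ÷ (*ps*). The true value is (1 − 0.95³)/0.05 = 0.142625/0.05 = 2.85, because three doses carry more risk than one.

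| *s* | Recorded per dose | Recorded per person, PEP++ vs control | Ratio per person |
|---|---|---|---|
| 0.1 | (1.9/3)/0.1 = 6.3 | 9.25% vs 0.50% | 18.5 |
| 0.3 | (2.1/3)/0.3 = 2.3 | 10.17% vs 1.50% | 6.8 |
| 0.5 | (2.3/3)/0.5 = 1.5 | 11.08% vs 2.50% | 4.4 |
| 0.9 | (2.7/3)/0.9 = 1.0 | 12.90% vs 4.50% | 2.87 |

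The ratio per dose does not depend on *p*. With *p* = 0.02 or 0.10 the ratios per person are similar (18.8 and 18.0 at *s* = 0.1). The distortion disappears in the last row, where capture is equal.

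**The case against.** The strongest reply is that this is a condensed article. The recording rule is one summary sentence, and its causal phrase may be loose wording. The article does not say that unattributed events are discarded, that field staff make the judgement, or that the form lacks a causality field. Fig. 1, protocol version 9.0 and the supplementary checklist are not shown, and any of them could list safety contacts in the control arm. This stands in full against the point about contacts, which is therefore conditional. It stands only in part against the point about attribution: there the article states a rule, and that rule as worded does not serve the task given to the committees.

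A reader might also infer three stronger conclusions that the document does not support:

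- That the trial plans a comparison of safety between arms. It plans monitoring in each arm; Table 3 has no safety test or estimate. Frequencies kept by arm still invite comparison.
- That only PEP++ has visits after dosing. Both arms have the two-year visit. What differs, on the visible text, is scheduled contact in the weeks after a dose.
- That the frequencies are not comparable, by some known factor. Any factor simply reflects the capture rates assumed, and it is 1 per dose if capture is equal.

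Finally, the remedy is partial. Self-report is not a neutral channel, since a contact who expects a return visit may wait for it. Which dose an event followed may also be partly recoverable already, because dated dose forms are linked by each contact's identification code.

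**Conclusion.** The concern holds in limited form. As worded, the rule puts causal attribution before registration in an open-label trial. Counts by arm then depend on that judgement, and an unattributed event may never reach the committee. This follows from the text alone, provided the sentence means what it says.

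Frequencies by arm may also not be comparable because of unequal early contact: two contacts against none in the visible text. This rests on there being no further safety contacts in Fig. 1 or the full protocol. Its size is unknown. The recorded ratio per dose of 6.3 down to 1.0 is an assumed range, not an estimate for this trial.

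No figure in the document is wrong on this point. It is an inexpensive improvement to safety recording.

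**What to change.** Reword the sentence in Data collection so that every adverse event after any dose is registered regardless of suspected cause. Make three items separate fields on the form:

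- causality;
- the preceding dose;
- the reporting route: observed at supervised dosing, self-reported, or elicited at a return visit.

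Where the committee sees the arms side by side, show events after the first dose within the same number of days in both arms, broken down by reporting route. Show events elicited at the dose 2 and dose 3 visits separately, as PEP++ only. If Fig. 1 or the full protocol already provides early safety contacts for control participants, say so in the text.

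The cost is a few fields on the existing form, changed committee tables and more forms for minor unrelated events. No visits are added and no treatment changes. The change does not remove all differential reporting and does not cover events after the third PEP++ dose, for which the text states no early contact. Both should be stated as limitations.
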